## Abstract

**Background:**

The current academic literature suggests there is a potential for using gardening as a tool to improve children’s fruit and vegetable intake. This study is two parallel randomised controlled trials (RCT) devised to evaluate the school gardening programme of the Royal Horticultural Society (RHS) Campaign for School Gardening, to determine if it has an effect on children’s fruit and vegetable intake.

**Method/Design:**

Trial One will consist of 26 schools; these schools will be randomised into two groups, one to receive the intensive intervention as “Partner Schools” and the other to receive the less intensive intervention as “Associate Schools”. Trial Two will consist of 32 schools; these schools will be randomised into either the less intensive intervention “Associate Schools” or a comparison group with delayed intervention. Baseline data collection will be collected using a 24-hour food diary (CADET) to collect data on dietary intake and a questionnaire exploring children’s knowledge and attitudes towards fruit and vegetables. A process measures questionnaire will be used to assess each school’s gardening activities.

**Discussion:**

The results from these trials will provide information on the impact of the RHS Campaign for School Gardening on children’s fruit and vegetable intake. The evaluation will provide valuable information for designing future research in primary school children’s diets and school based interventions.

**Trial registration:**

ISRCTN11396528

## Background

The impact of poor nutrition in children is causing major public health concerns across the globe [1]. Fruit and vegetables are a fundamental component of a healthy diet[2]. Currently, children’s consumption of fruit and vegetables is low in the United States of America, Australia and most European countries,[3-5] with the average intake of fruit and vegetables for children in the UK being around 2.5 servings per day[6]. In British children the main source of energy intake is from chips, biscuits and crisps,[6] highlighting the need for public health interventions to improve children’s overall dietary habits[7].

Epidemiological evidence indicates that a diet rich in fruit and vegetables can decrease the risk of developing cardiovascular disease, stroke, hypertension, type 2 diabetes mellitus, obesity and several forms of cancer[1,8]. A diet low in fruit and vegetable intake is one of the top ten risk factors for global mortality[9]. Research has also revealed that dietary habits are developed in childhood and persist throughout life; therefore it is vital that children at a young age consume adequate levels of fruit and vegetables[10,11]. Several studies indicate that children’s fruit and vegetable intake is positively associated with parental consumption[12].

Of particular public concern is the rise of obesity in children[13]. National surveys state that approximately one in ten children under the age of ten is obese, further estimates predict that 80% of children who are obese at the age of 10 to 14 will remain obese into adulthood[14]. Diet plays a fundamental role in weight management, having a healthy diet rich in fruit and vegetables, which are low energy density foods, could help tackle this epidemic[15].

Several different nutrition education programmes have been developed for schools, home and community settings in an attempt to improve children’s diets[15-22]. Evidence suggests that the most effective interventions are multi-component with both school and home based components [23,24]. Successful intervention studies have included a variety of components; integrating teaching about fruit and vegetables into the curriculum, training teachers in theories of behaviour change and nutritional education, increasing fruit and vegetable availability at school and in school meals, training of catering staff (verbal encouragement), hands-on exposure (tasting and preparation sessions), parental involvement through newsletters and homework activities, whole school approach (developing a nutrition policy, evening activities) and community involvement (local fruit and vegetable industry)[20,23-30]. These intervention programmes report a moderate increase in children’s fruit and vegetable consumption of approximately one third of a portion of fruit and or vegetables [22,31,32].

The use of school gardens as an education tool in schools is a relatively new approach to improve children’s diets. The theory behind using a school or community garden to improve children’s diets is that it provides children with the opportunity to learn about how fruit and vegetables are grown in an interactive manner[33], taking the focus away from classroom based nutrition education by using external support or a trained teacher.

The British Nutrition Foundation conducted a review of the psychosocial basis of food choice to provide evidence to explain how to influence food choice in children[34]. The main findings of relevance to young children were: the ‘one size fits all’ approach to intervention design does not seem to work well in any setting; and tailoring and message reinforcement appears to be important for sustained interest in the intervention programme. This is relevant from a school gardening perspective which requires repeated attention to prepare the ground, plant, tend and harvest. Several studies have indicated that the concept of familiarisation is important for children. Studies suggest that consumption of fruit and vegetables can be promoted if children are exposed to ‘healthier’ foods via teaching, through peer modelling, via the cafeteria and in vending machines. For example, children who were introduced to new foods using ‘hands-on’ activities in the classroom were 3–20 times more likely to subsequently choose and eat these foods in the canteen than children who did not have prior exposure[35-37].

This study will evaluate the Royal Horticultural Society (RHS) “Campaign for School Gardening.” This programme was launched in 2007 and since then has recruited over 11,500 primary schools. The main aims of the programme are to encourage schools to be involved in growing fruit and vegetables, to enrich the curriculum activities of the school, and to educate children with the values of gardening such as “healthy living” and “sustainability of the natural world [38].” This study will use two parallel randomised controlled trials to provide data on whether the RHS Campaign for School Gardening has an impact on fruit and vegetable intake in the diets of children. It will clarify the nature of any impact and provide important information on whether and how the children’s diets may be improved.

## Research questions

The following research questions apply to both Trials 1 and 2:

· Can the RHS Campaign lead to increases in vegetable and fruit intake in children aged 8–9 years?

· Does the RHS Campaign affect children's intake of other food and drink e.g. savoury snacks, confectionery products, soft drinks?

· What is the effect of the RHS Campaign on intake of key nutrients (fat, carbohydrate, protein, vitamin C, carotene, iron, sodium, folate)?

The effectiveness of either intervention would be determined by an increase in mean intake in one of the following; mean intake of fruit, mean intake of vegetables, or mean intake of fruit and vegetables at follow-up after adjusting for baseline.

## Methodology

### Sampling and recruitment of schools

#### Trial 1 – intensive vs. Less intensive intervention

The RHS plan to establish their Campaign for School Gardening to schools in the London region in the autumn of 2009. The RHS Campaign provides intensive support in each region to 10 schools through support from an RHS School Gardening Regional Advisor (the intensive intervention). The remaining schools will have access to support through twilight training sessions for staff and other activities (the less intensive intervention).

Twenty-six schools will be recruited from four boroughs in London: Wandsworth; Tower Hamlets; Greenwich; and Sutton. Of the 26 schools we will randomly allocate 10 schools to receive the intensive intervention and 16 schools to receive the less intensive intervention. The allocation sequence will be generated by the trial statistician. All schools will be allocated at the same time. Time between notification of allocation and the start of the intervention will be as short as possible. It will not be possible to randomise schools to receive no intervention at all since the RHS is committed to providing support to all schools who register an interest in the Campaign. As a consequence of this, we will recruit a second set of schools into a linked trial.

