#### Trial 2 – less intensive vs. Delayed intervention

Following selection of schools into trial 1, we will contact schools from neighbouring boroughs in London: Lewisham; Lambeth; Merton and Newham. We anticipate that these boroughs will have approximately 130 primary schools. We will aim to recruit 32 schools into the second trial. Of these schools, 16 will be randomly allocated to sign up to the RHS Campaign for School Gardening and to receive the less intensive intervention and 16 schools will act as comparison schools. The schools will be randomly allocated to the associate (i.e. less intensive) intervention or the comparison group. The comparison schools will have no active RHS intervention during the trial. They will be offered delayed access to the less intensive intervention at the end of the study.

It will not be possible to blind schools to their intervention group because of the nature of the intervention. The fieldworkers will be blinded to the allocation of schools to the intervention (more or less intensive) and comparison arms of the study.

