### Randomisation

Cluster randomisation with school location and borough to identify each “cluster” will be used to randomise the schools. The schools will be randomised by their London borough location using Stata[39]. They will be randomly assigned, for trial one to the intense RHS intervention or the less intense RHS intervention; for trial two to the less intense intervention or the delayed intervention (comparison). If the schools had more than one Year 3 or Year 4 class, the same statistical method will be used to determine which class should be involved in the trial.

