### Statistical analysis

Baseline child-level variables between the two intervention groups will be assessed for the following variables:

School level:

· % children with English as an additional language

· % non-white children

· % children with free school meals eligibility

· % children defined as having special educational needs

Child level:

· Sex

· Age

· Each of the primary and secondary outcomes

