### Primary analyses

A random or fixed intercepts model of primary and secondary outcomes will be used allowing for hierarchical structure of data caused by cluster randomisation: child within class within school. MLwiN [47] will be used for this analysis. The single covariate for the intervention group will be included in the model (treated as a random effect since schools in the trial are themselves a random sample from the population of schools).

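### Trial 1 draws its 26 schools in one batch with borough the only balancing factor named; constraining the draw on two listed school characteristics, and adjusting for them, would be a cheap improvement

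*Protocol article*

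**What the plan says.** All places are in the protocol article.

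- **Trial 1 – intensive vs. Less intensive intervention:** "Of the 26 schools we will randomly allocate 10 schools to receive the intensive intervention and 16 schools to receive the less intensive intervention", and "All schools will be allocated at the same time".
- **Trial 2 – less intensive vs. Delayed intervention:** "We will aim to recruit 32 schools into the second trial", of which 16 get the less intensive programme and "16 schools will act as comparison schools". Recruitment comes later: "Following selection of schools into trial 1, we will contact schools from neighbouring boroughs in London". No sentence says that these 32 schools are allocated in one batch.
- **Randomisation:** "The schools will be randomised by their London borough location using Stata". No other balancing factor is named for either trial.
- **Statistical analysis:** four school-level percentages are listed for comparison between groups: English as an additional language, non-white pupils, "children with free school meals eligibility", and special educational needs.
- **Primary analyses:** "The single covariate for the intervention group will be included in the model".
- **Research questions** and **Proposed outcome measures:** effectiveness is judged on follow-up intake adjusted for baseline. The model under Primary analyses does not show this adjustment.

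**The concern.** When every school is allocated at once, the whole list can be examined before the draw, so the allocation can be restricted on more than borough. The article names school characteristics that it considers worth comparing, but gives them no role in the draw or in the primary model.

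With 10 against 16 schools, one draw can leave the arms visibly apart on deprivation or language mix. A difference in fruit or vegetable intake would then be harder to credit to the programme. Trial 1 is the more exposed: its intensive arm cannot exceed 10 schools, so extra precision has to come from design and analysis.

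**Working it through.** **The plan's own figure.** The Proposed sample size section gives SD 85 g and ICC 0.125 for vegetables, a 0.5 portion difference, 90% power and a design effect of 6.6. Assume 80 g per portion (not stated) and 5% two-sided. Then n = 2 × (1.960 + 1.282)² × 85² / 40² = 94.9, rounded up to 95, and 95 × 6.6 = 627, as stated. The 5% level is inferred; 1% would give about 887. The vegetable and fruit design effects look exchanged (1 + 49 × 0.125 = 7.1; 1 + 49 × 0.114 = 6.6). That is a separate matter and does not enter below, where the ICC is used directly.

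**Starting power.** With 75% of 50 children completing, 37.5 per school, the variance of a school mean is 85² × (0.125 + 0.875/37.5) = 7225 × 0.1483 = 1072, SD 32.7 g.
- 10 v 16: SE = 32.7 × √(1/10 + 1/16) = 13.2 g. The ratio 40/13.2 = 3.03 on 24 df gives power of about 83%.
- 16 v 16: SE = 32.7 × √(2/16) = 11.6 g. The ratio 3.46 on 30 df gives about 92%.

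The between-school share of this variance is 0.125/0.1483 = 84%. That is a ceiling on what school characteristics could explain, not an estimate of what they do explain.

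**Chance imbalance.** The SE of a standardised difference in a school characteristic is √(1/k₁ + 1/k₂).
- Trial 1: 0.403. P(|difference| > 0.5 SD) = P(|Z| > 1.24) = 21.5%. At least one of two independent characteristics: 1 − 0.785² = 38%.
- Trial 2: 0.354. P = 15.7%. At least one of two: 1 − 0.843² = 29%.

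Simulated borough-stratified draws give the same (about 38–39% and 29–30%). The assumed borough sizes were 7, 7, 6, 6 with 3, 3, 2, 2 intensive schools for Trial 1, and four boroughs of 8 with 4 per arm for Trial 2. Taking the draw from the best-balanced tenth of allocations reduces the chance to about 0%.

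**Power without baseline intake in the model.** Simulation for vegetables: 40 g effect, 5% two-sided, school means with borough terms. R² is the assumed share of between-school variance that the two characteristics explain.

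| R² | Trial 1, borough only | Trial 1, constrained + adjusted | Trial 2, borough only | Trial 2, constrained + adjusted |
|---|---|---|---|---|
| 0% | 81.5% | 81.0% | 91.6% | 91.7% |
| 20% | 81.3% | 87.7% | 91.4% | 95.2% |
| 40% | 82.6% | 94.3% | 91.0% | 98.5% |

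Much of the gain comes from the adjustment. In a separate run for Trial 1 at 40%, power was 83.1% with neither change, 87.4% with the constrained draw alone, 91.3% with adjustment alone and 93.8% with both.

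**Power with baseline intake in the model.** Assume a correlation of 0.5 over time between the school effects that the characteristics do not explain. The change from adding both measures is then about −2 to +3 points in Trial 1 and about nil to +1 in Trial 2. If instead the total school effects correlate 0.5 or 0.7, Trial 1 goes from 86.6% to 87.7% or stays at 94.1% at R² of 20%. At 40% it goes from 88.1% to 94.0% or from 93.2% to 95.8%. A gain near 6 points thus needs both the 40% share and a baseline that carries little further information.

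**The case against.** Randomising 26 and 32 schools by borough is a valid, accepted design, and chance imbalance is already reflected in the standard error. The article also intends to adjust for baseline intake, which would absorb much of any stable difference between schools. Detailed covariate lists are commonly left to an analysis plan. The 0.5 SD threshold is a choice, and characteristics that correlate with each other and with borough go out of balance less often. For all four listed variables, the chance that at least one exceeds 0.5 SD falls from 62% and 50% (Trials 1 and 2, independent variables, simple draw) to about 47% and 34% if they correlate 0.4 and borough carries 30% of their variance. The chance of exceeding 0.75 SD is then about 13% and 6%.

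Most of this stands, and it rules out several stronger readings that a reader might infer:
- **That power is being lost for free.** The article gives no link between these characteristics and intake. At R² = 0 nothing is gained.
- **That large imbalance is likely.** For two characteristics the chance is below one half, at a moderate threshold.
- **That the plan cannot correct for imbalance.** The baseline adjustment named under Proposed outcome measures would do part of this, although Primary analyses omits it.
- **That both trials are drawn in one batch with the school data to hand.** The batch sentence stands under Trial 1 only, and the article does not say when the characteristics are obtained. Borough stratification itself is the likely reading of a loosely worded section.

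What the objection does not remove is that the article positively names the balancing factor and the single model covariate, and neither uses the characteristics it lists.

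**Conclusion.** The point holds as a design improvement and not as an error. In roughly 4 in 10 Trial 1 draws, at least one of two school characteristics would differ by more than 0.5 SD; a constrained draw makes that close to 0%. In Trial 2 the figure is about 3 in 10, and the remedy applies there only if allocation is also in one batch. The imbalance figures assume two independent, roughly normal characteristics and the borough sizes above.

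The power benefit is conditional. Trial 1 goes from about 82% to 88–94% without baseline intake if 20–40% of between-school variance is explained, with no gain at 0%. With baseline intake the change is mostly within −2 to +3 points. The argument is therefore mainly about balance and credibility, strongest for the capped 10 v 16 comparison. Priority is low to moderate.

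**What to change.** 1. Before the Trial 1 draw, obtain two variables from the list under Statistical analysis and name them in advance, for example the percentages for free school meals and for English as an additional language.
2. Keep borough as the stratum. Enumerate or sample the borough-stratified allocations, score each for balance on the two variables, and draw at random from the best 10%. With the assumed borough sizes there are 35² × 15² = 275,625 allocations, so a tenth still leaves ample randomness.
3. Put the same two variables in the primary model as fixed covariates, together with the baseline intake that Research questions and Proposed outcome measures call for, and correct Primary analyses to say so. Constraining without adjusting makes the test conservative: in simulation with four balancing variables that predicted intake, type I error fell to about 1–3% at a nominal 5%.
4. Do the same in Trial 2 if its schools are allocated together, and state whether they are.

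The cost is some programming, the need to have the two variables before the draw, and two school-level degrees of freedom. Two variables are preferable to four: adjusting for four that predict nothing lowered Trial 1 power from about 83% to 80–81% even with a constrained draw. No extra schools are needed.

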#### Trial 2 – less intensive vs. Delayed intervention

Following selection of schools into trial 1, we will contact schools from neighbouring boroughs in London: Lewisham; Lambeth; Merton and Newham. We anticipate that these boroughs will have approximately 130 primary schools. We will aim to recruit 32 schools into the second trial. Of these schools, 16 will be randomly allocated to sign up to the RHS Campaign for School Gardening and to receive the less intensive intervention and 16 schools will act as comparison schools. The schools will be randomly allocated to the associate (i.e. less intensive) intervention or the comparison group. The comparison schools will have no active RHS intervention during the trial. They will be offered delayed access to the less intensive intervention at the end of the study.

It will not be possible to blind schools to their intervention group because of the nature of the intervention. The fieldworkers will be blinded to the allocation of schools to the intervention (more or less intensive) and comparison arms of the study.

### Study population

#### Trial 1 inclusion criteria

All primary schools within the following London boroughs: Wandsworth; Tower Hamlets; Greenwich; and Sutton with classes in key stage 2 (years 3–6) will be invited to take part in the study.

#### Trial 2 inclusion criteria

All primary schools within the following London boroughs: Lewisham; Lambeth; Merton and Newham with classes in key stage 2 (years 3–6) will be invited to take part in the study.

### Exclusion criteria common to both trials

Independent schools, special schools and schools without all 4 year groups in key stage 2 at primary school (years 3–6) and small schools with less than 15 pupils/year group will be excluded.

### Proposed sample size

Cluster randomisation will be used, randomising at the school level, because the intervention will involve whole schools and participating classes. Based on results from our previous work on schools in a national sample, we estimate the standard deviation for the amount of vegetables eaten to be 85 g and for fruit 143 g. The associated intraclass correlation coefficient for total vegetables from Project Tomato was 12.5% and for fruit 11.4% (unpublished results). This sample of 50 children (one year 3 class and one year 4 class) from each school, will give a design effect of approximately 6.6 for vegetables and 7.1 for fruit to take account of the cluster randomisation. To have 90% power to detect a 0.5 portion difference in vegetable intake, 627 per group are required, i.e. about 13 schools using 2 classes from each school. To have 90% power to detect a 1 portion difference in fruit intake, 482 per group are required, i.e. about 10 schools. Based on results from our evaluation of the School Fruit and Vegetable Scheme, 75% who completed the Child And Diet Evaluation Tool (CADET) at baseline also completed the final follow up CADET. To allow for this margin of safety, 16 schools per group will be selected in each group apart from the intensive intervention group where it is only possible for 10 schools to be involved. The size of effect the study is powered to detect, (one half of a portion of vegetables or one portion of fruit) was chosen because it was considered the smallest improvement in intake that was worthwhile detecting with the achievable sample size, and considering the nature of the intervention.

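### The design effects for vegetables and fruit are swapped relative to the stated ICCs, so 627 and 482 children per group do not follow from those ICCs

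*Protocol article*

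**What the plan says.** Everything needed is in one paragraph of the protocol article, under Proposed sample size.

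- ICCs, from an unpublished source: "intraclass correlation coefficient for total vegetables from Project Tomato was 12.5% and for fruit 11.4" (per cent).
- Cluster size: "This sample of 50 children (one year 3 class and one year 4 class) from each school".
- Design effects: this cluster size "will give a design effect of approximately 6.6 for vegetables and 7.1 for fruit".
- Standard deviations: "we estimate the standard deviation for the amount of vegetables eaten to be 85 g and for fruit 143 g".
- Requirement for vegetables, at 90% power for half a portion: "627 per group are required, i.e. about 13 schools using 2 classes from each school".
- Requirement for fruit, at 90% power for one portion: "482 per group are required, i.e. about 10 schools".

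The paragraph then cites 75% retention from an earlier evaluation and sets 16 schools per group as a margin of safety. The intensive group is the exception, limited to 10 schools.

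**The concern.** Both outcomes use the same number of children per school, so the outcome with the larger ICC must have the larger design effect. The text pairs the larger ICC (vegetables) with the smaller design effect. Either the two ICCs or the two design effects carry the wrong labels.

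Vegetables need more schools than fruit and so set the size of the trial. If the ICCs are right, the vegetable requirement is the one understated, and the margin claimed for 16 schools is measured from too low a base. Because the ICCs are unpublished, a reader cannot settle the matter elsewhere, and anyone planning a later school trial from this paragraph could carry the wrong values forward.

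**Working it through.** **Inputs from the Proposed sample size section:** SD 85 g (vegetables) and 143 g (fruit); ICC 0.125 and 0.114; m = 50 children per school; power 90%; differences of 0.5 portion (vegetables) and 1 portion (fruit); 75% retention; 16 schools per group, 10 in the intensive group.

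**Assumptions, not stated in that section:** one portion = 80 g, so the differences are 40 g and 80 g; two-sided 5% test, so (1.960 + 1.282)² = 10.507. Portions of 75 and 85 g, a one-sided 5% test and a two-sided 1% test were also tried. Only 80 g with two-sided 5% reproduces both printed totals.

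**Step 1. Design effects, DE = 1 + (m − 1) × ICC**

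| Outcome | ICC | DE computed | DE printed |
|---|---|---|---|
| Vegetables | 0.125 | 1 + 49 × 0.125 = 7.125 | 6.6 |
| Fruit | 0.114 | 1 + 49 × 0.114 = 6.586 | 7.1 |

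The printed values are the right numbers attached to the wrong outcomes. This step uses neither assumption.

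**Step 2. Reproducing the plan's totals.** Unclustered n per group = 2 × SD² × 10.507 / difference².

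- Vegetables: 2 × 85² × 10.507 / 40² = 94.9, rounded up to 95. Times the printed 6.6 = 627.0. Printed: 627.
- Fruit: 2 × 143² × 10.507 / 80² = 67.1, rounded up to 68. Times the printed 7.1 = 482.8. Printed: 482.

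So the design effects were used in the calculation as printed.

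**Step 3. Totals on the ICCs as printed**

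- Vegetables: 95 × 7.125 = 676.9, so 677 per group; 677 / 50 = 13.5, so 14 schools. Against 627 this is +8%.
- Fruit: 68 × 6.586 = 447.8, so 448 per group; 448 / 50 = 8.96, so 9 schools. Against 482 this is −7%.

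**Step 4. Power for vegetables.** SE = 85 × √[DE × (1/(k₁m) + 1/(k₂m))], where k₁ and k₂ are schools per group; power = Φ(40/SE − 1.960). For 13 against 13 schools of 50 with ICC 0.125, SE = 85 × √(7.125 × 2/650) = 12.585 g, 40/SE = 3.178, and power = Φ(1.218) = 88.8%. With 25% loss, m = 37.5 and DE = 1 + 36.5 × 0.125 = 5.56 (5.16 for ICC 0.114).

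| Schools | Children per school | ICC 0.125 (as printed) | ICC 0.114 (if labels swapped) |
|---|---|---|---|
| 13 v 13 | 50 | 88.8% | 91.1% |
| 16 v 16 (Trial 2) | 50 | 94.1% | 95.6% |
| 16 v 16 (Trial 2) | 37.5 | 93.3% | 94.8% |
| 10 v 16 (Trial 1) | 50 | 87.1% | 89.6% |
| 10 v 16 (Trial 1) | 37.5 | 85.8% | 88.2% |

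At exactly 627 children per group with DE 7.125, power is 87.7%. It differs from 88.8% only because 13 × 50 = 650. With a t reference on the number of schools minus 2, the 13 v 13 figure at ICC 0.125 is 86.2% (24 df), and Trial 2 after loss is 91.7%.

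For fruit with ICC 0.114, Trial 1 has 96.9% at 50 per school and 96.3% at 37.5, so fruit is not at risk.

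**The case against.** The mispairing itself is not disputed. The case against making much of it has four parts.

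1. *The document cannot show which pair is wrong.* If the ICC labels are the slip, 627 and 482 are correct. This stands: both totals are wrong only relative to the ICCs as printed. Either way, one printed pair of numbers is wrong.

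2. *No group has 13 schools.* Trial 2 uses 16 against 16 and keeps about 93% after loss even on the less favourable reading. Trial 1 is capped at 10 intensive schools and falls below 90% on either reading; the swap moves its vegetable power by about 2.5 points. The fruit error is on the safe side. This also stands, and it limits the practical harm. It does not rescue the stated requirement, and Trial 1's vegetable power cannot be stated from this text until the ICCs are settled.

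3. *The t-based 86% at 13 schools mixes two effects.* The plan's totals come from the normal approximation. With no swap, the t-based power at 13 schools is already 88.7%, and 14 schools at ICC 0.125 give 88.8%. This is fair. The part due to the swap is best read from the normal figures: 91.1% down to 88.8%.

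4. *The 80 g portion and the 5% level are not stated.* True. The only test level the article prints is 1%, under its secondary and subgroup analyses. Both values are assumptions, supported by reproducing both totals. The swap in the design effects depends on neither.

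**Conclusion.** The point holds. At 50 children per school the printed design effects contradict the printed ICCs, and neither rounding nor another common cluster size can explain it. The contradiction was carried into the required sample sizes for primary outcomes.

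If the ICCs are as printed, the vegetable requirement is understated by 50 children per group (677 against 627) and one school (14 against 13), and the fruit requirement is overstated by 34 children (448 against 482) and one school. If the ICC labels are swapped, the totals stand and the ICCs need correcting. These sizes rest on the 80 g portion and the two-sided 5% test. The planned recruitment for Trial 2 is adequate on either reading. Trial 1 is below 90% for vegetables on either reading, mainly because of the 10-school cap.

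**What to change.** Check the two ICCs against the source data, then do one of the following.

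- If they are as printed, change the design effects to 7.1 (vegetables) and 6.6 (fruit), the children per group to 677 and 448, and the schools per group to 14 and 9.
- If the ICC labels were swapped, print 11.4% for vegetables and 12.5% for fruit, and keep 627 and 482.

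In either case, state the portion weight and the test level used in the calculation. Restate power at 37.5 completers per school for 16 against 16 (Trial 2) and 10 against 16 (Trial 1). For vegetables that is about 93% and 86% with ICC 0.125, or 95% and 88% with ICC 0.114, by the normal approximation.

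The cost is a look-up and one corrected paragraph. Recruitment for Trial 2 does not change, and the number of intensive schools in Trial 1 is fixed by what the programme can support.
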